## Abstract

**Background:**

Insomnia disorder exhibits complex manifestations and heterogeneous clinical trajectories. Accurate subtyping of insomnia might enhance understanding of its clinical presentations and facilitate precision management. The Digital Multi-modal approaches to Subtyping Insomnia disorder (DIMOSI) study is a national prospective cohort study utilizing multi-modal assessments to explore the subtypes of insomnia disorder, their natural trajectories, and related mental health outcomes.

**Methods:**

A total of 4,000 adult participants meeting International Classification of Sleep Disorders, 3rd Edition (ICSD-3) criteria for insomnia disorder will be recruited from community or clinical settings. Eligible participants will be invited to complete the multi-dimensional assessments via a digital platform, including a structured interview, questionnaires, cognitive tasks, sleep-activity diary, physiological characteristics, and ecology momentary assessments, as well as 7-day physical activity and sleep tracking using wearable devices. All participants will be followed up at 6 and 12 months. The primary outcome is the identification of multi-modal subtypes of insomnia disorder and their correlates. Secondary outcomes include the longitudinal trajectories of these subtypes, associated risk factors, and mental health outcomes.

**Results:**

As of June 30, 2025, a total of 2937 patients with insomnia disorder have been recruited, with a mean age of 37.3 years (SD = 12.6), 59.3% from outpatient clinics, and 66.5% female. Among the participants, 2850(97.1%) were suffering from current insomnia disorder, while the mean score of the ISI was 15.5 ± 5.8. A total of 2134 participants (72.7%) wore accelerometers, while 2429 (82.7%) wore wearable EEG monitors for continuous assessments.

**Discussion:**

The DIMOSI study is a large-scale national prospective cohort investigating insomnia disorder utilizing a self-developed digital multi-modal platform. It integrates comprehensive subjective and objective assessments from 33 centers in China. The current study offers a unique opportunity to explore subtypes of insomnia disorder and their natural course and their correlates through the digital multi-modal platform that provides enriched and comprehensive assessments. It may provide the potential to inform the development of personalized prevention and intervention strategies, ultimately improving patient outcomes.

**Trial registration:**

Clinical Trial Registry Name: Digital Multi-modal approaches to deep phenotyping insomnia disorder. Registration Number: ChiCTR2200056425. Date of Registration: 2022-02-05.

**Supplementary information:**

The online version contains supplementary material available at 10.1186/s12888-025-07648-9.

## Background

Insomnia symptoms affect 19%-50% of adults globally [1], with approximately 10% meeting the criteria for insomnia disorder [2]. Patients with insomnia disorder often experience impaired quality of life and general health [2], along with various adverse outcomes, including coronary heart disease, depression, and increased risk of self-harm and suicidality [3, 4]. Insomnia disorder imposes a significant burden not only on patients but also on their families and society [5, 6]. Community-based studies have shown that the 5-year persistence rate for insomnia symptoms ranges from 32.6% to 42.5% [7]. Even with adequate treatment, such as pharmacotherapy or cognitive behavioral therapy for insomnia (CBTI), approximately 20%-40% of patients respond poorly, likely due to heterogeneity in pathogenesis and clinical presentations [8–10]. Therefore, to overcome the limitations in the assessment and treatment of insomnia disorder, it is crucial to establish accurate subtypes based on comprehensive assessments for its core features and related characteristics [11, 12]. Multi-modal subtyping insomnia disorder could empower the development of sleep medicine by informing not only insomnia diagnosis and symptomatic management but also prognostic prediction and personalized intervention selection.

Significant efforts have been made in recent decades to clarify the diverse manifestations of insomnia disorder. First, the most commonly used classification in general clinical practice is based on nocturnal complaints [2] according to the International Classification of Sleep Disorders - Third Edition (ICSD-3) [7, 13]. Clinicians typically prescribe hypnotics with different half-lives based on difficulty initiating sleep (DIS), difficulty maintaining sleep (DMS), or early morning awakenings. However, over half of patients with insomnia disorder report at least two types of nocturnal symptoms, and the stability of this classification system is often unsatisfactory [8, 14]. Second, Vgontzas and colleagues have found that insomnia with objectively short sleep duration as measured by a single-night nocturnal polysomnography (PSG), may represent a more biologically severe subtype with a diminished response to CBTI compared to insomnia without short sleep duration [15]. However, PSG requires overnight hospitalization, which is costly, time-consuming, and limits scalability [16]. Third, recent studies have attempted to use emotional processing and cognitive functions to subtype insomnia disorder [12], but their application in clinical practice remains underexplored. Finally, a recent effort using portable sleep assessments extracted insomnia-related subtypes from a large-scale cohort, but clinical interpretations of these subtypes were not provided [17].

Taken together, previous studies have proposed several subtypes of insomnia disorder based on subjective and objective measures [18–20]. However, subtyping methods that rely solely on subjective reports are easy to implement but will lack objective indicators, resulting in ambiguous classifications. On the other hand, subtyping based on PSG monitoring is limited in capturing the temporal and spatial fluctuations of sleep in insomnia. Moreover, the current classification schemes for insomnia provide limited guidance for clinical treatment [21]. This classification challenge is closely tied to the high heterogeneity of insomnia disorder. In the current study, we plan to integrate the data of sleep and circadian rhythm, mental distress, behavior, and cognitive function, from both subjective reports and long-term ambulatory monitoring.

The rapid advancement of digital technology over the last decade has revolutionized mental health care, providing new opportunities for the assessment and management of mental disorders [22–25]. Wearable devices, including smartphones and accelerometers (Axivity AX3), have emerged as tools to monitor sleep and circadian rhythm, capturing changes in physical activity, environment, and related mental status simultaneously [26, 27]. However, few assessment platforms have integrated subjective and objective measurements, for insomnia disorder. To systematically assess core features of insomnia disorder and its related characteristics, an integrated digital platform, called Zhiyoumian (知优眠 in Chinese, meaning “know and improve your sleep”) was established for this study, consisting of two apps and a website for comprehensive assessments.

The Digital Multi-modal Approaches to Subtyping Insomnia Disorder (DIMOSI) study (ChiCTR2200056425 in Chinese Clinical Trial Registry) is designed to address the critical gaps, including: (a)providing objective and continuous data to complement subjective reports, (b) capturing dynamic, real-world fluctuations rather than the single-night PSG assessment, and (c) simultaneously assessing multiple functional modalities to create a holistic profile. We hypothesize that the integration of multi-modal digital data, including clinical interview, self-report, ecological momentary assessment (EMA), data from wearable devices, and cognitive tasks, may capture the interaction between the behavioral, emotional, circadian, and cognitive systems that underlie insomnia heterogeneity, leading to a precise subtype system of insomnia disorder. The DIMOSI aims to achieve the following: (a)exploring the subtypes of insomnia disorder using comprehensive multi-modal assessment approaches, (b) validating the stability and predictive accuracy of the identified subtypes through a prospective study with follow-up assessments at 6 months and 12 months (c)determining the natural trajectories and related mental health outcomes of different subtypes of insomnia disorder. This fine-grained, data-driven subtyping study for insomnia disorder is anticipated to transcend unstable, symptom-based classifications and accelerate the development of clinical paradigm (Fig. 1).

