### Study population

To determine the subtypes of insomnia disorder and explore their predictive value for trajectory and intervention outcomes, an estimated 40–80 variables will be included in the statistical model. Based on an estimated events per variable (EPV) of 50 to ensure sufficient statistical power, a total of 4,000 participants are required at the baseline [28].

Participants aged 18–65 years with a lifetime history or current insomnia disorder will be recruited. Subjects will be included in the study if they meet the following inclusion criteria: a. Previously or currently meeting the diagnostic criteria for insomnia disorder in ICSD-3; b. Ability to read and understand Chinese, and use the devices required for the study; c. Ability to provide informed consent. The exclusion criteria are: a. Lifetime history of schizophrenia, intellectual disability, or severe physical illness; b. Pregnancy or lactation; c. current involvement in other clinical research projects.

As of June 2025, 33 study sites specializing in psychiatry, neurology, or sleep medicine have taken part in the current study. The principal research centre of the DIMOSI study is located at the Guangdong Mental Health Centre, Guangdong Provincial People’s Hospital (Guangdong Academy of Medical Sciences), Southern Medical University, Guangzhou, China. Additionally, 33 study sites across various regions of China have joined as collaborative institutes (Fig. 2).

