**Fig. 2 Fig2:**
[figure not shown]
Geographic distribution of the 33 collaborative study sites across China

All individuals participating in the study are permitted to continue their ongoing treatments and medications, which will be recorded and documented throughout the research. In addition, electronic Cognitive Behavioral Therapy for Insomnia (e-CBTI), a routine fee-based clinical service delivered via a smartphone application, was optionally accessible to participants; for those who opted in, the study team covered the service fee without modifying the treatment content or delivery.

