#### Longitudinal modeling

We will use classification and regression methods to investigate whether baseline information can predict follow-up outcomes. Chi-square analysis, repeated measures analysis, and mixed-effects models will be employed to examine the relationships among the cross-sectional data and the changes over time across different visits. For binary outcomes (e.g., the occurrence of anxiety or depression), logistic regression models will be used, while linear regression models will assess continuous outcomes (e.g., changes in the Insomnia Severity Index (ISI) score). Mixed-effects models will analyze longitudinal changes while accounting for individual variability.

Statistical methods may be adjusted as needed based on the actual data, and we will adopt the most appropriate methods for the analyses. Any limitations in the analysis will be thoroughly addressed and elaborated upon in subsequent research publications.

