## Results

In the current study, 127 researchers across study sites received consistent training in clinical interviews, the use of wearable devices, and other psychological assessments. We randomly selected 46 researchers to complete a reliability assessment for 8 clinical structural interviews. The Cochran’s Q values ranged from 29.2 to 43.0, with all p-values > 0.05, indicating a high consistency among interviewers.

From November 28, 2022, to June 30, 2025, approximately 5000 individuals with suspected insomnia disorder were screened. A total of 3134 participants were interviewed, of whom 2937 (93.7%) were recruited and 197 (6.3%) were excluded. Among those recruited, there are 1743 (59.3%) from outpatient clinics and 1194 (40.7%) from community settings. The most common reason for exclusion was psychotic symptoms resulting from other mental disorders, which led to the inability to complete the clinical interview. The recruitment procedure is shown in Fig. 3.

All participants met the ICSD-3 criteria for insomnia disorder, with a mean age of 37.3 ± 12.6 years and 1952 (66.5%) were females. At baseline, 2850 participants (97.1%) were suffering from current insomnia disorder as defined by the clinical interview based on ICSD-3. In terms of comorbidities, assessed by the structured clinical interviews administered via the Zhiyoumian-Researcher app, 505 participants (17.2%) had current depressive disorders, and 613 participants (20.9%) had current anxiety disorders. The mean score of the ISI was 15.5 ± 5.8, with a median (interquartile range) score of 16.0 (7.0). When comparing those from the community setting and clinic, we found that the participants from the clinic are significantly older than their counterparts. But there is no statistical difference in sex, comorbidities, and insomnia severity (Table 2).

**Table 2 Tab2:** Demographics, comorbidities, and insomnia severity in participants from community and clinic settings（*N* = 2937）

	Community(*n* = 1194)	Clinic（*n* = 1743）	*p*
Age, mean±SD	35.9±12.3	38.2±12.3	＜0.001
Gender Female, n(%)	780 (65.3%)	1172 (67.2%)	0.283
Comorbidities, n(%)	364 (30.5%)	484 (27.8%)	0.115
Depressive Disorder	212(17.8%)	293(16.8%)	0.518
Generalized Anxiety Disorder	270(22.6%)	343(19.7%)	0.058
Bipolar Disorder	39(3.3%)	48(2.8%)	0.439
Panic Disorder	15(1.3%)	25(1.4%)	0.748
Post-Traumatic Stress Disorder	25(2.1%)	45(2.6%)	0.460
ISI, mean±SD	15.7±5.84	15.3±5.79	0.101
ISI ≥ 8, n(%)	1104(92.5%)	1602(92.9%)	0.625

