Note: ISI, Insomnia Severity Index

In this EMA study, a total of 1231 participants (76.6%) provided eligible data for at least 50% of the time points, 1015 participants (63.2%) for at least 75%, and 746 participants (46.4%) for at least 90%. Furthermore, 2134 participants (72.7%) utilized accelerometers, while 2429 (82.7%) wore wearable EEG monitors for continuous assessments of their physical activity and sleep patterns. Of the 2850 participants with current insomnia, 2455 received e-CBTI treatment. Detailed data cleansing and analysis of the objective data will be reported elsewhere.

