## Conclusions

The DIMOSI study is a national multicentre prospective cohort study utilizing an integrated digital assessment platform, conducted among adult patients with insomnia disorder. This study provides a unique opportunity to explore the subtypes of insomnia disorder, which hold predictive value for the clinical trajectories and treatment responses.

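### Aim (c) promises natural trajectories, but 86.1% of current cases received optional e-CBTI with the fee covered by the study, and the plan names no treatment variable

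*Protocol article*

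**What the plan says.** **The aim.** In the Background, aim (c) is "determining the natural trajectories and related mental health outcomes of different subtypes of insomnia disorder". The Background paragraph of the Abstract also says natural trajectories, and its Discussion paragraph says natural course. The Methods paragraph of the Abstract words the secondary outcome as longitudinal trajectories, without *natural*.

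**Treatment outcomes.** The sample-size text under Study population says the study will "explore their predictive value for trajectory and intervention outcomes, an estimated 40–80 variables will be included in the statistical model". The Conclusions describe the subtypes as ones "which hold predictive value for the clinical trajectories and treatment responses".

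**Treatment during the study.** The paragraph after Figure 2 lets participants continue their treatments and medications, which are recorded. It adds that e-CBTI, a routine fee-based service, "was optionally accessible to participants; for those who opted in, the study team covered the service fee".

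**Uptake.** The Results state: "At baseline, 2850 participants (97.1%) were suffering from current insomnia disorder as defined by the clinical interview based on ICSD-3". Later they state: "Of the 2850 participants with current insomnia, 2455 received e-CBTI treatment".

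**Analysis.** Longitudinal modeling lists chi-square, repeated-measures, logistic, linear and mixed-effects methods. On change over time it says: "Mixed-effects models will analyze longitudinal changes while accounting for individual variability". Strengths and limitations says that sleep medication at baseline was recorded and controlled for by unspecified statistical techniques. The limitations do not mention e-CBTI.

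**The concern.** A natural course is the course without the intervention under discussion. Here most current cases received an active insomnia therapy. They chose it themselves, and the study removed its price. What the cohort will show at 6 and 12 months is a course under treatment.

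This matters most for comparisons between subtypes. A subtype whose members opt in more often, or benefit more, will look as though it has the better prognosis. The Background itself gives reason to expect unequal benefit: it reports a diminished response to CBTI in insomnia with objectively short sleep. A random effect for the individual removes none of this. Reported under the label of aim (c), a treatment difference could be read as a property of the subtype.

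**Working it through.** **1. The document's own figures.** Current cases: 2850/2937 = 97.04%, printed as 97.1%. This is a rounding slip with no bearing here. Target sample: 80 variables × 50 events per variable = 4,000, which reproduces. The document gives e-CBTI counts but no percentage.

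**2. Uptake (counts from the Results).**
- Received e-CBTI: 2455/2850 = 86.1%.
- Did not: 2850 − 2455 = 395, or 13.9%.
- The 395 are an upper limit for untreated current cases, because other treatment may continue.

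**3. Cases without e-CBTI per subtype.** The number of subtypes k is left to the data, so k and an even split are assumptions. At the full target with unchanged shares (also an assumption), current cases are 4,000 × 2850/2937 ≈ 3,882, and those without e-CBTI are 3,882 × 395/2850 ≈ 538. All figures are before dropout.

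| k | To date (395/k) | At 4,000 (538/k) |
|---|---|---|
| 3 | 132 | 179 |
| 4 | 99 | 134 |
| 5 | 79 | 108 |

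**4. What an unadjusted subtype trajectory estimates.** For subtype j, let m_j be the mean change without e-CBTI (under whatever other treatment continues), u_j the uptake, and e_j the mean e-CBTI effect among recipients. Then

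observed change_j = m_j + u_j × e_j,

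and the difference between two subtypes is (m_1 − m_2) + (u_1 e_1 − u_2 e_2). Only the first bracket could be called prognosis without e-CBTI.

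**5. Illustrative size.** The document gives no e-CBTI effect and no uptake by subtype, so effects of 2, 4 and 6 ISI points and uptake gaps of 10 and 20 percentage points are assumptions. The overall shift is effect × 0.861. With equal effects, the false gap between subtypes is effect × uptake gap.

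| Assumed effect | Mean shift | False gap, 10 points | False gap, 20 points |
|---|---|---|---|
| 2 | 1.7 | 0.2 | 0.4 |
| 4 | 3.4 | 0.4 | 0.8 |
| 6 | 5.2 | 0.6 | 1.2 |

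Against the reported baseline ISI SD of 5.8, the false gaps run from 0.2/5.8 = 0.03 to 1.2/5.8 = 0.21 SD. With identical uptake but effects that differ by an assumed 2 points between subtypes, the gap is 0.861 × 2 = 1.7 points, or about 0.3 SD.

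**The case against.** **The article is condensed.** Longitudinal modeling names no covariates at all, not even age, sex or site, so its silence on treatment may be a summary's silence. A reader might infer that the models will contain no treatment term. The document does not support that, and a fuller plan could hold one. What can be said is that none is named here. The conflict between aim and uptake remains, because no covariate list makes this cohort untreated.

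**Treatment is not wholly ignored.** Control for baseline sleep medication is claimed. That stands, but it covers neither e-CBTI nor treatment during follow-up.

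**The 395.** A reader might take them as an untreated comparison group. They are self-selected and may use other treatment.

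**Treatment response.** A reader might infer that no work on it is possible without an untreated group. That goes too far. Predicting outcome by subtype among e-CBTI recipients is legitimate prognostic work. An untreated comparison is needed only for a subtype-specific treatment effect, which the document does not explicitly claim and which is not one of its three aims.

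**Size.** The effects, uptake gaps and number of subtypes are assumed. The Results give no timing, amount or completion of e-CBTI, and the false gaps from unequal uptake alone are modest. This limits the magnitude but does not remove the mislabelling.

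**Conclusion.** The point holds as a conflict within the document. The Abstract and aim (c) promise a natural course, while 2455 of 2850 current cases (86.1%) received self-selected e-CBTI whose fee the study covered for those who opted in. Followed as written, the study would report a treated course as a natural one, and subtype differences would mix prognosis, treatment effect and uptake.

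The 86.1% and the ceiling of 395 rest on printed counts. The shifts in ISI points rest on assumed effects and show scale only. The finding concerns a secondary objective. Subtype identification, the primary outcome, is not shown to be affected.

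**What to change.** 1. In the Background and Discussion paragraphs of the Abstract and in aim (c), replace *natural* with trajectories observed under ongoing treatment with optional study-funded e-CBTI. The secondary outcome in the Methods paragraph of the Abstract does not use the word and can stay.
2. Report e-CBTI uptake by subtype.
3. Present subtype trajectories adjusted for, and stratified by, e-CBTI receipt and recorded medication. Label the stratum without e-CBTI as exploratory.
4. In the Conclusions, word treatment responses as prognosis among e-CBTI recipients, not as a subtype-specific treatment effect.
5. List self-selected e-CBTI among the limitations.

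**Cost.** This needs a few changes of wording and some added analyses. Medication is already recorded and e-CBTI receipt is already counted. With 2,937 of 4,000 recruited by June 2025, the change can precede the longitudinal analysis.

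**Downside.** The aim becomes less ambitious, the strata without e-CBTI are small, and confounding by self-selection remains. Start of e-CBTI may itself depend on earlier symptoms, so a time-varying term in an ordinary mixed model would not recover the natural course. Adjusted results should not be presented as if it did.

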**Fig. 1 Fig1:**
[figure not shown]
Conceptual model of multimodal digital subtyping for insomnia disorder

## Methods

The Digital Multi-modal Approaches to Subtyping Insomnia Disorder (DIMOSI) study is a national prospective cohort study recruiting 4,000 individuals with a lifetime history of insomnia disorder from both clinical and community settings. Clinical setting includes outpatient clinics of psychiatry neurology, and sleep, while the individuals recruited from community health centers, promotional posters, and social media are recognized to be the participants from community setting. Participants will be invited to complete assessments via a digital platform, which includes data collection through smartphones, accelerometers, (Axivity AX3) and the wearable electroencephalogram (EEG) monitors for the comprehensive multi-modal evaluation of insomnia disorder and its related characteristics at baseline and follow-up points.

